3. Educational resources. We will provide information on training in cognitive behavioural therapy and counselling, and we will develop e-learning courses. We will provide resources for volunteers who need to improve their communication with depressed patients.

4. Data systems. We will develop a comprehensive website, with educational resources and tools for health-care professionals, patients and relatives.

Figure 2 illustrates how the various components in the package target various levels of the health-care system.

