Based on previous studies [40,41] we anticipate that between 40% and 60% of GPs will consent to data collection. All GPs that consent to participate will be asked to mail a questionnaire to each of the six patients that have been identified. Patients will be asked to complete and return the questionnaire by mail. If a patient consents to participate in the study, but does not wish to complete the questionnaire, we will ask the patient to appoint a family member to answer on their behalf if possible. Alternatively the patient may choose to consent to being contacted and interviewed by telephone.

The following data will be collected from patients:

• The patient’s assessment of improvement for depression, anxiety, sleep problems, physical activity, problem-solving, social contact and loneliness (secondary outcome measures)

• Adherence to medication

Each patient, GP and municipality included in the study will receive a unique study ID, which is available to the research group. A list at each GP practice will couple the patient’s study ID and the patient’s national ID number. We will use the patient ID numbers generated by the GPs’ electronic medical records systems. It will be possible for GPs to identify patients using these numbers, but the investigators will not have access to information identifying the patients, unless they first return a mailed consent form with the questionnaire. All communication (for example, letters) with patients will otherwise be through the patients’ GP.

We will collect the following descriptive data from GPs: age, sex, years of clinical experience as a GP, whether they are a specialist in primary-care medicine, competency in using CBT (collected during the structured interviews) and the number of elderly patients (65+) on the patient list.

A schematic presentation of participant timeline and time schedule for data collection is presented in Additional file 1: Appendix E.

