### Statistical methods

The primary outcome of interest for our analysis is the mean adherence rate per GP (based on six patients). We will assess the number of recommendations that were followed with regard to the severity of depression, and we will calculate an overall mean for adherence across disease severity for each GP. For mild and moderate depression there are seven recommendations and for severe depression there are two recommendations; these will be assessed by interviewing the GP, who will have access to patients’ medical records during the interview. The analysis will be performed as an intention-to-treat analysis; we count all GPs in the group to which they were assigned, regardless of whether they received the intervention or not.

All analyses will be performed in SAS version 9.2 (SAS Institute Inc.) using PROC GLIMMIX with random effects for municipality and practice to account for the clustered nature of the data. Continuous data will be analysed assuming that the data follows a normal distribution (linear regression) and dichotomous data will analysed using the binomial distribution (logistic regression). In the initial analyses only the allocation to intervention or control will be included as an independent variable in the analysis (Intervention = YES/NO).

The following factors and variables are assumed to be effect modifiers: whether the municipality already has a collaborative plan (may improve adherence), whether access to cognitive behavioural therapy is poor (may reduce adherence), whether municipalities belong to the ‘Centre for Development of Institutional and Home Care Services’ network (may improve adherence) and whether GP has many elderly patients on the list (may improve adherence).

Each of the pre-specified effect modifiers will be separately included as independent variables (alongside allocation to intervention or control) in the model. All the effect modifiers with *P* < 0.3 in the previous step will be included as independent variables in a final multivariate model.

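### The four named effect modifiers enter only as main effects, and a P < 0.3 screen then picks the final model's covariates, so effect modification is not tested and no model is named primary

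*Protocol article*

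**What the plan says.** The analysis is set out in the protocol article under Statistical methods, in three steps.

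1. A mixed model is fitted "using PROC GLIMMIX with random effects for municipality and practice to account for the clustered nature of the data". At first it holds allocation alone: "In the initial analyses only the allocation to intervention or control will be included as an independent variable in the analysis".
2. Four variables are introduced with "The following factors and variables are assumed to be effect modifiers": an existing municipal collaborative plan, poor access to CBT, membership of a development-centre network, and a GP list with many elderly patients. Each carries an expected direction, for example "whether the municipality already has a collaborative plan (may improve adherence), whether access to cognitive behavioural therapy is poor (may reduce adherence". They are then fitted one at a time: "Each of the pre-specified effect modifiers will be separately included as independent variables (alongside allocation to intervention or control) in the model".
3. All those with P < 0.3 "in the previous step will be included as independent variables in a final multivariate model".

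The article describes no product term, interaction test or subgroup contrast, and calls no model primary. The Randomisation section stratifies municipalities by population size and by the proportion of inhabitants aged 80 or older. Neither factor is mentioned in the analysis.

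**The concern.** An effect modifier changes the size of the intervention effect. A variable fitted beside allocation, without a product term, gets a coefficient that describes its association with adherence averaged over the two arms. That is a prognostic question. The directions given for the four variables are prognostic too, since they say how adherence itself would move.

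Two things are at stake. First, a P-value reported under the label of effect modification could be read as showing where the package works better or worse, and the Objectives section says the trial is meant to inform decisions about improving care. Second, the covariates of the last model depend on outcome data, and the reader is not told whether that model or the allocation-only model carries the conclusion.

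**Working it through.** **The plan's own figures.** Inputs from Sample size: 80 municipalities, 10.93 GPs each, 50% consent, six patients per GP, difference 0.05, SD 0.17, ICC 0.02, alpha 0.05 (taken as two-sided).

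- GPs: 10.93 × 80 × 0.5 = 437.2. Patients: 437 × 6 = 2,622. Both agree with the article.
- With equal clusters of 5.465 GPs, the design effect is 1 + 4.465 × 0.02 = 1.089 and the effective n per arm is 437.2 / 1.089 / 2 = 200.7. SE = 0.17 × √(2/200.7) = 0.0170, and power = Φ(0.05/0.0170 − 1.96) = 0.838.
- With the design effect based on all 10.93 GPs (1.199), power is 0.802, which matches the stated 0.80. The present point does not depend on which variant was used.

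**What the planned coefficient measures.** Write adherence as b0 + b1·T + b2·Z + b3·T·Z, with T for allocation and Z for a two-level modifier. Effect modification is b3. If T·Z is left out and the arms are equal, the coefficient of Z estimates b2 + b3/2. It is zero when b2 = −b3/2, however large b3 is, and non-zero whenever b2 is non-zero with b3 = 0.

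**Simulation of the stated procedure.** 10,000 trials per scenario, run on municipality means. Assumptions: equal cluster sizes, four independent modifiers each with 50% prevalence, none affected by allocation.

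| Scenario (average intervention effect 0.05) | Modifier kept at P < 0.3 | Interaction test significant at 0.05 |
|---|---|---|
| Interaction 0.10, no average effect of modifier | 27% | 82% |
| No interaction, modifier predicts adherence by 0.05 | 97% | 5% |
| Neither | 30% | 5% |

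The screen responds to prognosis and is blind to the interaction.

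**Dependence on the data.** Four variables, each in or out, give 2⁴ = 16 possible final models. If all four were unrelated to adherence and independent, at least one would still pass with probability 1 − 0.7⁴ = 0.76 (simulated 0.758).

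**Effect on the allocation test.**

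| Scenario | Allocation only | After selection |
|---|---|---|
| Type I error, no modifier matters | 0.050 | 0.053 |
| Type I error, one modifier with main effect 0.10 | 0.053 | 0.051 |
| Power for 0.05, no modifier matters | 0.828 | 0.824 |

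The Monte Carlo error of these type I rates is about √(0.05 × 0.95 / 10,000) = 0.002. With a true effect of 0.05, the mean estimate after selection was 0.050.

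**Power of a proper interaction test.** For a municipality-level modifier of prevalence p, SE = 0.0170 / √(p(1 − p)).

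| p (assumed) | SE | Power, interaction 0.05 | Power, interaction 0.10 |
|---|---|---|---|
| 50% | 0.034 | 0.31 | 0.84 |
| 10% | 0.057 | 0.14 | 0.42 |

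**Where each variable would come from (Data collection).** The collaborative plan and network membership are in the municipal baseline list. The number of elderly patients is listed among the GP descriptive data. CBT access is not in the baseline list. The only CBT item listed is the GP's "competency in using CBT (collected during the structured interviews"), and those interviews follow the intervention.

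**The case against.** The strongest reply is that little harm follows. Allocation is randomised, so screening covariates on their own P-values barely touches the allocation effect, and the simulation bears this out. An unselected, allocation-only analysis is already fixed, and it matches the two-group comparison behind the power calculation. Effect modification is not a stated objective, and the given directions suggest prognostic covariates under the wrong name. All of this stands. It limits the point to labelling and model choice, and it makes relabelling a legitimate remedy.

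Three stronger readings are tempting and should not be drawn.

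- *The selected model inflates type I error or biases the effect.* The article gives no ground for this, and under the assumptions above neither was seen.
- *About three trials in four would be harmed.* The 0.76 is how often a chance covariate enters when none of the four matters. It is not error in the intervention effect, and the article itself expects each variable to matter.
- *The analysis will adjust for a consequence of the intervention through GP competency in CBT.* The article names access to CBT as the modifier and lists competency as descriptive data; nothing says that one will stand in for the other. On training, the package promises this: "We will provide information on training in cognitive behavioural therapy and counselling". That is information, not CBT training itself. The appendices are not shown, and a source for CBT access may be there.

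It may also be said that an article leaves detail to an analysis plan. Here, though, the steps are stated, and they do not do what their label says.

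**Conclusion.** The point holds in a limited form. As stated, the procedure cannot detect effect modification, because it contains no interaction. This follows from the model itself and needs no assumption. The final model's covariate set is one of 16 chosen from outcome data, and no model is named primary. The consequences are mislabelled inference and room for choice after the data are seen. Distortion of the intervention effect is not shown.

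The simulation and power figures rest on assumptions outside the article: prevalences of 10% to 50%, independent modifiers, equal cluster sizes in the simulation, and all four variables treated as municipality-level, although list size belongs to the GP. The simulation also assumes modifiers unaffected by allocation, so it gives no reassurance about a variable recorded after the intervention.

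**What to change.** 1. Name one primary model in advance: allocation with the randomisation strata as fixed covariates, keeping the random effects for municipality and practice. Keep the allocation-only model as a named supporting analysis if wanted.
2. Drop the P < 0.3 step.
3. Choose one of two routes for the four variables. Either fit each in its own model with its main effect and its interaction with allocation, and report the interaction estimate with its confidence interval as exploratory, given the low power. Or rename them prognostic covariates and fix the adjustment set in advance.
4. Use only variables measured before the intervention or not affected by it. For the collaborative plan this means the baseline item, because the presence of a plan is also a secondary outcome. Take CBT access from a pre-intervention source or omit it, and do not replace it with the competency item from the GP interviews.

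The cost is a rewording of Statistical methods and a few more model runs. No new data are needed, except a pre-intervention source for CBT access if that variable is kept.

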### Ethics

The intervention is a package of strategies targeted at municipal officials and health-care professionals with the aim of improving the delivery of recommended care to elderly patients with depression, and ultimately patient outcomes. Municipalities and GPs in the intervention group will be free to choose whether to use any of the intervention material that will be sent to them and GPs will be free to choose whether to participate in outreach visits or courses. Consequently, no consent is required prior to the intervention. Informed consent from GPs will be sought prior to data collection, which will take place after the intervention.

GPs will be given an identification number and all data collected from GPs will be stored, analysed and reported anonymously. The investigators will not collect information that enables them to identify individual patients unless a patient first gives written informed consent to a telephone interview, and all patient information will also be stored, analysed and reported anonymously. The participants may withdraw their consent at any time. This project has been approved by the Regional Ethical Committee of the South-Eastern region of Norway (file no 2013/572b).

## Discussion

This cluster randomised controlled trial will investigate whether a tailored implementation approach is an effective strategy for improving health-care professionals’ practice towards elderly patients with depression in primary care. The interventions target several prioritised determinants of practice. We will measure the overall effect of the implementation interventions as the proportion of GPs’ actions that are consistent with the recommendations. There is a risk of acquiescence bias when asking GPs whether they followed the recommendations. We intend to ask each GP about their treatment of the identified patients, and then check if the recommendations were followed or not. Thus, whether the GP is aware of the recommendations has less impact. The intervention is complex, and it will be difficult to identify the specific effect of each strategy in the intervention. The addressed determinants of practice were prioritised from hundreds of suggested determinants. Thus, there is a risk that, although we prioritised the determinants according to a common protocol for the TICD project, other determinants that we did not prioritise might, in fact, have a significant impact on practice. The planned process evaluation will explore these issues. The process evaluation will indicate whether we have identified the most important determinants and been able to develop and implement interventions that effectively address each of those determinants. To the extent that the interventions are not successful, the process evaluation will indicate if we have not identified or prioritised the most important determinants, or why the interventions did not adequately address the determinants that were identified.

## Trial status

The TICD project has been running since 2011, and will be concluded by the end of 2014. The intervention is planned to start autumn 2013.

## Endnotes

^a^For these recommendations, we will consider the recommendation implemented if the GP discussed the problem with the patient and the patient did not have the problem or if the patent had the problem and was offered advice

^b^We will use PGI to assess any improvement in sleep problems, anxiety and problem-solving.

## Abbreviations

CBT: Cognitive behavioural therapy; CGI-I: Clinical Global Impression Scale – improvement; GP: General practitioner; HADS: Hospital anxiety and depression scale; HCP: Health-care professional; ICC: Intra-class correlation coefficient; ICD-10: International statistical classification of disease and related health problems, 10th revised edition; ICPC-2: International classification of primary care, 2nd edition; PGI: Patient global impression – improvement; RCT: Randomised controlled trial; TICD: Tailored implementation for chronic diseases.
